**5.0 Sample size**

A total of 50 old, active men will be recruited; participants will be separated into 2 groups of 25 and each group will receive either SUPP or PLB. Previous studies have shown that supplementation with creatine monohydrate during RE training in older adults can increase dynamic strength by approximately 1.75 – 3.25 kg more than RE training alone. Using this effect size and a standard deviation of 1.5 kg, n = 20 subjects are needed to detect a difference with α = 0.05 and β = 0.8 using a two-way ANOVA. To account for the possibility of increased variability in the sample set and allowing for a potential 20% dropout rate, a conservative number of 25 subjects per group was chosen.

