**6.0 Design**

The overall study design is depicted in Figure 1, below. Participants will be placed in either the SUPP or PLB group, depending on their strength, fat-free mass and body mass index.

[figure not shown]

**Figure 1**. Study schematic. D_2_O, deuterium oxide; 1RM, 1 repetition maximum; VO_2peak_, peak oxygen consumption; OGTT, oral glucose tolerance test; QOL, quality of life assessment, PA, physical activity

*6.1 Assessments*

Approximately 1 week prior to beginning the study, participants will receive a muscle biopsy from *vastus lateralis*, exercise and physical function testing, body composition analysis, an OGTT, and an executive function and quality of life assessment (see Figure 1). These tests will take place over the course of 3-5 days during the same week. During the week these assessments are taking place, participants will complete a 3-day food diary and physical activity log at home, as well as wear an accelerometer (mounted on an arm band) to estimate daily caloric intake, macronutrient distribution and energy expenditure. We will assess glomerular filtration rate (GFR), an estimate of kidney function, by examining cystatin C concentrations in blood samples collected during pre, mid and post-study testing periods.

These assessments will be repeated during week 7, and again upon completion of the study during week 19. Exercise tests (1RM and VO_2peak_) will be repeated at weeks 11 and 15 to ensure an adequate exercise stimulus is maintained during training. The assessments at week 7 and week 19 include serial muscle biopsies for the measurement of the acute satellite cell response to exercise. Details of the serial muscle biopsy protocol are described below. Participants will be asked to refrain from strenuous exercise, caffeine and alcohol for 48 hours prior to each assessment.

*6.2 Phase 1*

Phase 1 of the study is 6 weeks in duration and will be completed primarily at home. Participants will consume 2 study beverages per day – the first approximately 1 hour after breakfast, and the second before bed. Participants will be encouraged to maintain their normal diets and levels of physical activity. We will provide participants with all their study beverages at the beginning of the study.

*6.3 Phase 2*

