**9.0 Data analysis**

Data will be analyzed using a 2-way analysis of variance (ANOVA) with between (SUPP, PLB) and within (time) group comparisons. Tukey’s HSD post hoc testing will be used to assess differences between the means when interactions are detected. Statistical significance will be accepted at α<0.05.

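### Men are placed by strength, fat-free mass and BMI, but the planned group-by-time ANOVA adjusts for none of these, nor for the pre-study value, so precision is lost

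*Protocol*

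**What the plan says.** Protocol section 6.0 (Design) gives the allocation rule in one sentence: "Participants will be placed in either the SUPP or PLB group, depending on their strength, fat-free mass and body mass index". It describes no randomisation, pairing, strata or minimisation.

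Section 6.1 sets a full assessment about one week before the study starts and adds: "These assessments will be repeated during week 7, and again upon completion of the study during week 19". The 1RM and VO2peak tests are also done at weeks 11 and 15.

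Section 9.0 (Data analysis) names the model: "Data will be analyzed using a 2-way analysis of variance (ANOVA) with between (SUPP, PLB) and within (time) group comparisons". It continues: "Tukey’s HSD post hoc testing will be used to assess differences between the means when interactions are detected". No covariate is named. Section 9.0 does not say how missed visits are handled, although section 5.0 sets the sample size "allowing for a potential 20% dropout rate".

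Section 2.0 makes muscle strength, physical function and body composition the primary objective. Two of the placement variables, strength and fat-free mass, are therefore pre-study values of outcomes under test.

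**The concern.** When variables decide who goes into which group, the analysis should condition on them. There are two reasons.

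- **Precision.** If the variables predict the outcome and the groups have been balanced on them, the true sampling error of the group difference is smaller than the unadjusted model reports. Intervals are then too wide and the test rejects too rarely.
- **Bias.** If the placement leaves the groups different on these variables, an unadjusted contrast carries part of that difference into the estimate.

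The interaction in section 9.0 compares changes from the pre-study value. That amounts to subtracting the whole baseline (a slope of 1) instead of letting the data estimate the slope. With about 20 men per arm expected to complete, the lost precision matters, and recovering it needs no new data. An SAP could add covariates only by departing from the model that section 9.0 names.

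**Working it through.** **Inputs from the protocol.** Two groups of 25; 20% dropout; visits before the study and at weeks 7 and 19; group-by-time ANOVA; α = 0.05.

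**Inputs assumed.** Correlation ρ between pre-study and follow-up values: 0.5, 0.7 and 0.9. Equal variance σ² before and after training.

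**The plan's own figure.** The dropout step reproduces: 20/(1 − 0.20) = 25 per group. The 20 itself does not reproduce as a per-arm number at 80% power: 2 × (1.96 + 0.842)² × (1.5/1.75)² = 11.5, so 12 per arm. That is a separate matter, and nothing below depends on it.

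**Step 1: variance per man.**
- Change score: 2σ²(1 − ρ).
- Baseline-adjusted: σ²(1 − ρ²).
- Ratio, change over adjusted: 2(1 − ρ)/(1 − ρ²) = 2/(1 + ρ).

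| ρ | Variance ratio 2/(1+ρ) | SE ratio | Sample size needed with adjustment, (1+ρ)/2 |
|---|---|---|---|
| 0.5 | 1.333 | 1.155 | 75% |
| 0.7 | 1.176 | 1.085 | 85% |
| 0.9 | 1.053 | 1.026 | 95% |

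**Step 2: effect on the test if placement balances the baseline.** With perfect balance, the change contrast varies only as much as the adjusted one, but its model still reports the larger SE. A nominal 1.96 threshold then acts as 1.96 × √(2/(1+ρ)) = 2.263, 2.126 and 2.011. The two-sided tail areas are 2.4%, 3.4% and 4.4%.

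A simulation checks this: 4,000 trials per setting, 20 men per arm, three visits, σ = 1, no effect. Groups were either matched on the outcome's own baseline or random. Monte Carlo error near 5% is √(0.05 × 0.95/4000) = 0.34 percentage points.

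| ρ | Group-by-time ANOVA, matched | Change score, matched: model SE / actual SE | Baseline-adjusted, matched | Group-by-time ANOVA, random |
|---|---|---|---|---|
| 0.5 | 3.0% | 0.315 / 0.272 | 4.7% | 4.6% |
| 0.7 | 3.6% | 0.244 / 0.228 | 5.1% | 5.1% |
| 0.9 | 4.3% | 0.140 / 0.139 | 5.6% | 4.8% |

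The model SEs agree with the formula: √(2 × 2(1 − ρ)/20) = 0.316, 0.245 and 0.141. Under random allocation at ρ = 0.5 the change-score SE is right (model 0.314, actual 0.316), so the only loss there is efficiency.

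**Step 3: power.** For a true difference of 0.6 SD with matched groups, the group-by-time ANOVA rejects in 44.1%, 69.8% and 99.6% of trials at ρ = 0.5, 0.7 and 0.9. The baseline-adjusted test rejects in 56.1%, 74.4% and 98.7%. The gain is clear at 0.5, modest at 0.7 and absent at 0.9.

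**Step 4: if placement leaves the groups unequal.** With a baseline difference D and a regression slope of ρ, the follow-up difference expected without any treatment effect is ρD. The change contrast is then expected to be ρD − D = −(1 − ρ)D, that is 0.5, 0.3 or 0.1 of the baseline difference, in the direction opposite to it.

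**Step 5: partial data.** Let 20% of men lack one visit. An analysis restricted to complete rows has an SE about 3% larger than one using all data if week 19 is missing (ratios 1.035, 1.031 and 1.027). It is about 12% larger if only week 7 is missing (√(25/20) = 1.118).

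**The case against.** The strongest case against is that the planned ANOVA is a recognised method, and that in the balanced scenario it errs on the safe side: no extra false positives and a modest loss of power that vanishes at high ρ. Repeated 1RM or DXA values may well correlate highly, but the protocol gives no figure. Step 2 also assumes tight matching on the outcome's own baseline. Balancing three variables jointly would balance each less closely, and nothing shows that they predict satellite-cell, glucose, cognitive or renal outcomes. All of this stands, and it limits the size and certainty of the point.

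Four stronger readings are tempting, but the protocol does not support them.

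- *The analysis ignores baseline.* It does not. Baseline is a level of time, and the interaction compares changes from it. What is missing is its use as a covariate.
- *Men with a missed visit are discarded.* Section 9.0 does not say so. Classical repeated-measures ANOVA usually needs complete rows, but missing-data rules may stand in an SAP that is not shown. The 20% is a planning allowance, not a count of men to be excluded.
- *The error bars are simply too wide.* This requires that placement balanced a prognostic variable, and section 6.0 does not state how placement works.
- *Type I error falls to almost zero.* Rates of 2.4%, 0.8% and about 0% at ρ = 0.5, 0.7 and 0.9 belong to an unadjusted comparison of post-study means. The planned interaction test compares changes. Such rates could bear on a Tukey comparison between groups at one visit only if its error term included between-man variance, which the protocol does not fix.

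What remains is the mismatch between sections 6.0 and 9.0. Adjustment is a sound response in each of the three allocation scenarios.

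**Conclusion.** The point holds as a conditional matter of efficiency and calibration, worth correcting but not fatal. The model in section 9.0 omits the variables that section 6.0 uses to place men and does not use the pre-study value as a covariate.

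The SE of the change contrast is about 15%, 8% and 3% larger than the adjusted one at ρ = 0.5, 0.7 and 0.9, given equal variances. What else follows depends on the placement:

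- **Balanced on a prognostic baseline:** the interaction test is conservative, at about 3.0%, 3.6% and 4.3% instead of 5%.
- **In effect random:** the test is valid but less efficient.
- **Unequal groups:** the contrast may be biased by a fraction (1 − ρ) of the baseline difference.

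Adjustment removes that bias only so far as placement depended on the measured variables and the model for them is adequate. Keeping partial data is a secondary benefit, small in precision and resting on a missing-at-random assumption. It does not generally cure dropout that depends on unobserved response.

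**What to change.** In section 9.0, replace the 2-way ANOVA with a linear mixed model on all available post-baseline visits, containing:

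- group, visit and group-by-visit;
- the pre-study value of the outcome as a covariate;
- strength, fat-free mass and BMI as used for placement, omitting any that duplicates the outcome's own pre-study value (for example fat-free mass when that is the outcome).

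Report adjusted group differences with 95% confidence intervals. State which strength measure was used for placement, since section 7.1 lists six 1RM exercises. Do not constrain the two groups to a common baseline mean, because section 6.0 does not establish random allocation. Where an outcome has no pre-study value, as with the deuterated-water synthesis rates first measured at week 7, adjust for the placement variables alone.

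The cost is a change of wording, a little more analysis work and a few degrees of freedom. No new visit, measurement or participant is needed.

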**10.0 Recruitment**

Participants will be recruited from the Hamilton and surrounding area through the posting of study advertisement posters in newspapers and on the McMaster Campus (see Appendix 4). It is anticipated that all subjects will be unknown to the investigators. All subjects will review the consent form prior to receiving a signed copy. Participants will be encouraged to contact any of the investigators if they have any questions or concerns about the study. A copy of the signed consent form will also be added to the participants’ data file.

